### Statistics

In general data will be expressed as mean (standard deviation) in case of normal distribution, or median (interquartile range) in case of non-normal distribution.

## **8. Expected results**

- In this study we expect to find a more prominent effect of fluid challenges on cardiovascular parameters in patient with a Fontan circulation as compared to healthy controls.
- We expect that the use of enalapril in Fontan patients will exaggerate the responsiveness to central blood volume depletion and will increase the responsiveness to fluid challenge as well.
- We expect that the use of enalapril will result in a decreased aortic pulse wave velocity, a better cardiac autonomic profile and an increase in cardiopulmonary exercise stress testing.
- By evaluating the basic characteristics of patients who respond best on enalapril treatment with those who respond the least will probably result in the identification of a basic profile of those patients who will profit best of enalapril treatment.

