There are as yet no studies available that investigate the effect of ACE inhibition on various cardiovascular parameters in patients with a Fontan circulation. By studying the effect of ACE inhibition on cardiovascular parameters as systolic and diastolic ventricular function, cardiac output, and the sensitivity of the cardiovascular system to fluid changes the basic effects of ACE inhibition on the cardiovascular system of Fontan patients will become more clear. This will result in a more appropriate selection of patients that will profit most of the use of ACE inhibitors.

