##### Sample size calculation:

To detect statistical significant difference of our main study parameter  $VO_2\text{peak}$  (ml/kg/min), between Fontan patients before and after treatment with enalapril, we calculated a group size of 52 will be sufficient. We calculated this sample size for paired observations with a clinical relevant effect of 10% elevation after treatment, with a mean of 33.5 and SD of 6.8 before treatment (Bossers et al.; J Thorac Cardiovasc Surg 2014) and an elevation of the mean to 36.85 with an expected same SD after treatment and calculated a SD of the difference of 6.8 with a correlation coefficient of 0.5. We used an alpha of 0.01 with 80% power. We used a lower alpha of 0.01 to correct for multiple comparison according to the Bonferroni correction, because we have five main study parameters. Moreover, we also need to take the change of drop out into account, which means we need 55 patients per group when we expect a 5% drop out. This means a group size of in total 55 Fontan patients and a group of 55 healthy subjects will be sufficient.

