## **7. Data analysis**

The study has a cross-sectional between-subject design paired with prospective within-subject design. Baseline cardiovascular measurements will be compared between the Fontan patients and their age and gender matched healthy controls. Comparisons between the groups will be made using the independent T-test in case of normal distribution and Mann-Whitney U test in case of non-normal distribution (SPSS for Windows, recent version).

After a period of 3 months treatment with enalapril all baseline cardiovascular measurements will be repeated and compared to pre-treatment values (echocardiography, cardiopulmonary exercise stress testing, blood testing, 24-hour monitoring of electrocardiography and impedance cardiography, and aortic distensibility). Also the fluid challenge by passive leg raising as well as the depletion of central and splanchnic blood volume by head up tilt testing will be repeated and compared to pre-treatment values.

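### Looking for those who profit by comparing best with least responders loses information and mixes response with regression to the mean; a baseline-adjusted regression on all patients is the better exploratory analysis

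*Protocol*

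**What the plan says.** The last bullet of Protocol section 8 (Expected results) gives the only indication of how patients who benefit are to be found: "By evaluating the basic characteristics of patients who respond best on enalapril treatment with those who respond the least". The outcome is put as a hedged expectation, namely that this comparison "will probably result in the identification of a basic profile of those patients who will profit best of enalapril treatment". The bullet does not say which measurement defines response, where best ends and least begins, whether patients in between are left out, or which test is used.

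Section 7 (Data analysis) plans a before-after comparison: "After a period of 3 months treatment with enalapril all baseline cardiovascular measurements will be repeated and compared to pre-treatment values". It contains no responder analysis, and neither do the objectives in section 2 or the study parameters in section 6.

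The Enalapril part of section 1 presents selection of patients as the expected pay-off: "This will result in a more appropriate selection of patients that will profit most of the use of ACE inhibitors". The Summary says much the same.

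The only sample size is for the paired VO2peak comparison: "we calculated a group size of 52 will be sufficient". Allowing for loss of patients, the same section adds: "we need 55 patients per group when we expect a 5% drop out". No power is stated for the responder profile.

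**The concern.** A change in VO2peak, or in any other measurement taken before and after treatment, lies on a continuous scale. Contrasting a best group with a least group has two costs.

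- **Lost information.** A split at the median treats a patient just above it like the largest responder. A comparison of the extremes discards the patients in the middle. With about 52 patients there is little information to spare, and the profile depends on where the cut falls.
- **Regression to the mean.** A patient whose baseline reading happened to be low tends to show a large rise. Sorting on raw change therefore sorts partly on baseline, and a characteristic that goes with baseline can look like a predictor of response when it is not.

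Section 8 is the one place where the hoped-for selection of patients is given a method, so a false or missed profile would weaken that part of the study's message.

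**Working it through.** **1. The protocol's own sample size.** Inputs from section 4 (Sample size calculation): means 33.5 and 36.85, SD 6.8 at both times, before-after correlation 0.5, alpha 0.01, power 80%.

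- Difference: 36.85 - 33.5 = 3.35.
- SD of the difference: 6.8 × √(2 × (1 - 0.5)) = 6.8.
- Paired t-test, noncentral t, two-sided alpha 0.01: n = 52, power 80.5%. (Sidedness is not stated; two-sided reproduces the figure.)
- With 5% dropout: 52 / 0.95 = 54.7, so 55.

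The figure reproduces. It is a sample size for the mean change, not for a responder profile.

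**2. Power lost by grouping.** The protocol gives no correlation between a characteristic and the change, so a range is assumed. Further assumptions: 52 evaluable patients, one continuous characteristic, bivariate normal data, two-sided alpha 0.05, and 20,000 simulated trials per row (simulation error of each power at most √(0.25/20,000) = 0.35 points). Full scale is the correlation test on all 52. The splits are t-tests of the characteristic between best and least responders: 26 v 26, 17 v 17 and 13 v 13.

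| Assumed correlation | Full scale | Halves | Outer thirds | Outer quarters | Loss (points) |
|---|---|---|---|---|---|
| 0.20 | 29.7% | 20.2% | 23.7% | 23.5% | 6.0 to 9.5 |
| 0.30 | 58.5% | 40.3% | 47.6% | 46.9% | 11.0 to 18.3 |
| 0.38 | 81.4% | 61.2% | 69.8% | 69.2% | 11.6 to 20.2 |
| 0.45 | 93.3% | 77.3% | 84.9% | 84.9% | 8.4 to 16.0 |
| 0.60 | 99.8% | 96.8% | 98.8% | 98.8% | 1.0 to 3.0 |

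A separate run at 0.38 gave 80.5% against 59.7% for halves, a loss of 20.8, which is the upper end of about 21. Outer tenths lose up to about 32 points (at 0.40). At alpha 0.01 the losses for the three splits in the table run from about 3.5 to 26 points over correlations of 0.2 to 0.6.

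**3. Regression to the mean.** With equal SDs and before-after correlation ρ, the correlation of baseline with change is

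(ρ - 1) / √(2 × (1 - ρ)) = -√((1 - ρ)/2).

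With the protocol's ρ = 0.5 this is -√0.25 = -0.5. It holds when every patient has the same true response.

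Now take a characteristic that correlates q with measured baseline and is related to the post-treatment value only through it. Its correlation with change is -0.5 × q although it predicts nothing beyond baseline. For q = 0.6 this is -0.30, and the 0.30 row then gives the false-positive rate: about 40% to 48% for the three splits. Direct simulation gives about 40% to 49% at q = 0.6 and about 13% to 16% at q = 0.3. Regressing the post-treatment value on baseline and the characteristic gives 5% in both cases.

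The same row shows that a full-scale analysis of raw change without baseline would be wrong about 59% of the time at q = 0.6. The protection comes from the baseline term, not from continuity alone.

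**4. Power of the regression itself.** If the characteristic is unrelated to baseline and correlates 0.30 with change, removing baseline raises the correlation to 0.30 / √(1 - 0.25) = 0.346. Simulated power is 71%, against 40% to 48% for the splits.

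**The case against.** The strongest reply is that section 8 is not an analysis plan. The sentence is a hedged expectation with no cut and no test, and its loose wording does not exclude a regression. Details of an exploratory profile can sit in an analysis plan that is not shown. No power is claimed, so no stated figure is wrong.

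Much of this stands. What remains is that the sentence does name a form of comparison. A plan that followed it could choose only how much information to lose. The point concerns that form, not missing detail.

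A reader might go further in four ways that the protocol does not support.

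- **That section 7 already fixes the responder test.** Its sentence "Comparisons between the groups will be made using the independent T-test in case of normal distribution and Mann-Whitney U test" concerns Fontan patients against healthy controls at baseline. Nothing ties it to responders.
- **That selecting patients is a listed objective.** It is an anticipated benefit in the Summary and section 1, and is not among the objectives in section 2.
- **That the loss is one fixed figure whatever the cut.** It depends on a correlation, split and alpha that the protocol does not give.
- **That a regression would show who benefits from the drug.** All patients are treated and controls are measured once (section 3), so individual change also contains measurement variation and growth.

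A technical reservation also stands. The 5% error rate in step 3 assumes that the characteristic acts through measured baseline. If it follows only the stable part of a patient's level, raw change is not biased by it, and baseline adjustment can itself create an association.

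**Conclusion.** The point holds as a modest improvement. Best-versus-least grouping lost power in every scenario computed. The loss is about 6 to 21 points for halves, outer thirds or outer quarters at assumed correlations of 0.2 to 0.45, about 1 to 3 points at 0.6, and more for narrower extremes. These figures rest on 52 evaluable patients, two-sided alpha 0.05 and normal data.

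The correlation of -0.5 between baseline VO2peak and its change follows directly from the protocol's own inputs. VO2peak serves as the example because it is the only measure with figures; the protocol does not say that it defines response. The false-positive rates depend on how a characteristic relates to baseline, which is assumed.

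The sample size and the main before-after analysis are unaffected.

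**What to change.** Replace the best-versus-least wording in section 8, and add to section 7, for example:

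*As an exploratory analysis in all patients with both measurements, the post-treatment value is regressed on the baseline value and on each baseline characteristic, kept continuous where it is measured so. Slopes are reported with confidence intervals as associations, not as proof of drug benefit, because there is no untreated follow-up group. The baseline value of the measure itself enters as adjustment and is not read as a predictor of benefit. Patients are not divided into best and least responders.*

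The text should also name the measure or measures to which this applies.

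The cost is wording only: no extra patients, visits or procedures. The small downside is that results appear as slopes in place of a simple two-column responder table.

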## **SUMMARY**

**Rationale:** There is no consensus on the use of ACE inhibition in Fontan patients without ventricular dysfunction. Multiple centres prescribe enalapril on a routine base for patients with a Fontan circulation and a preserved ventricular function, while other centres have considerable doubt about its effectiveness. Too little research has been done to the effectiveness of ACE inhibition in Fontan patients. There are as yet no studies available that investigate the effect of ACE inhibition on various cardiovascular parameters in patients with a Fontan circulation. By studying the effect of ACE inhibition on cardiovascular parameters as systolic and diastolic ventricular function, cardiac output, and the sensitivity of the cardiovascular system to fluid changes, the basic effects of ACE inhibition on the cardiovascular system of Fontan patients will become more clear. This will result in a more appropriate selection of patients that will profit of the use of ACE inhibitors.

**Main objective:** To treat Fontan patients for 3 months with the ACE inhibitor enalapril and compare a set of cardiovascular measurements before and after treatment in order to study its effect on the cardiovascular system and the effect of a reversible fluid challenge and depletion in Fontan patients, and to correlate all these results with the results of a symptom limited maximal exercise test.

**Study design:** This study consists of a longitudinal intervention study and a cross-sectional study.

**Study population:** 55 patients with a univentricular heart after palliation with the Fontan circulation will be included from an age of 8 until 18 years old. Patients who already use enalapril will be excluded. A number of fifty healthy age and gender matched subjects will serve as controls.

**Intervention (if applicable):** To all Fontan patients enalapril will be given twice daily at a dose of 0,5 mg/kg/day with a maximum of 20 mg per day. All Fontan patients will undergo all the investigations before and after treatment and healthy controls will undergo all the investigations once, except for blood testing and the symptom limited exercise test which will not be performed in healthy controls.

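### Comparing best with least responders cannot show who profits from enalapril: with one value before, one after and no untreated Fontan group, baseline VO2peak can look predictive when the drug does nothing

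*Protocol*

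**What the plan says.** Section 8 (Expected results) names both a method and a conclusion. The method is "evaluating the basic characteristics of patients who respond best on enalapril treatment with those who respond the least". The conclusion is that this will probably yield a profile of the patients who gain most from the drug. The section does not define response or the characteristics to be compared.

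Two other places carry a matching expectation. The rationale in the Summary says "This will result in a more appropriate selection of patients that will profit of the use of ACE inhibitors", and the end of the enalapril part of section 1 says "This will result in a more appropriate selection of patients that will profit most of the use of ACE inhibitors".

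On design, section 5 gives enalapril to every Fontan patient. Section 3 has all measurements made at baseline and repeated after three months. Healthy controls are measured once, untreated and without an exercise test.

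The sample size paragraph in section 4 works "with a mean of 33.5 and SD of 6.8 before treatment" and "an elevation of the mean to 36.85 with an expected same SD after treatment". From these it "calculated a SD of the difference of 6.8 with a correlation coefficient of 0.5".

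**The concern.** The only individual response this design yields is the difference between two single measurements. That difference contains any drug effect, ordinary visit-to-visit variation and natural course over three months, and nothing in the design separates them.

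Sorting patients by it also creates a predictable artefact. A patient whose baseline happened to be low tends to rise, and one whose baseline happened to be high tends to fall. If baseline function is among the characteristics profiled, the best responders will tend to be those who started low, whether or not enalapril works.

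At stake is a selection profile for children aged 8 to 18, for a drug whose use in patients with preserved ventricular function section 1 describes as disputed.

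**Working it through.** **Inputs, all from the sample size paragraph in section 4.** Baseline mean 33.5, mean after treatment 36.85 (difference 3.35), SD 6.8 at both visits, correlation r = 0.5, alpha 0.01, power 80%, 52 evaluable patients.

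**Reproducing the plan's figures.**
- SD of the difference = √(2 × 6.8² × (1 − 0.5)) = 6.8, as stated.
- A paired t-test with difference 3.35, SD 6.8, two-sided alpha 0.01 and 80% power needs n = 52 (power 0.805), as stated. The plan does not give the sidedness; two-sided reproduces its figure.
- 52/0.95 = 54.7, so 55 with 5% dropout, as stated.

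The inputs below are therefore those the plan itself uses.

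**Assumptions added here.** Response is the change in VO2peak, values are bivariate normal, and best and least are the top and bottom thirds (17 v 17 of 52). Enalapril has no effect in any patient, so the mean is 33.5 at both visits.

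**Formulas at zero drug effect with equal SDs.**
- Correlation of baseline with change = −√((1 − r)/2). At r = 0.5 this is −0.50.
- Expected rise for a patient 1 SD below the mean = (1 − r) × 6.8. At r = 0.5 this is 3.4, against the 3.35 the plan calls clinically relevant.
- The slope of baseline on change is −1/2 for any r below 1.
- The mean change in an outer third is about ±1.09 × SD of change = ±1.09 × 6.8 = ±7.4. Mean baselines are then 33.5 − 3.7 = 29.8 (best) and 33.5 + 3.7 = 37.2 (least), a gap of 7.4.
- The chance of a rise above 3.35 is P(Z > 3.35/6.8) = 31%.

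**Simulation of 20,000 null trials of 52 patients at each r:**

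| r | Correlation of baseline with change | Baseline gap, best minus least third (ml/kg/min) | Gap significant at p<0.05 |
|---|---|---|---|
| 0.5 | −0.50 | −7.4 | 92% |
| 0.7 | −0.39 | −5.7 | 71% |
| 0.8 | −0.32 | −4.7 | 53% |
| 0.9 | −0.22 | −3.3 | 29% |
| 0.95 | −0.16 | −2.3 | 16% |

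The nominal rate is 5%.

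**What the artefact does not reach.** Write each measurement as a stable true level plus independent visit noise. Change is then the difference of two noise terms and is unrelated to the true level. A stable trait correlated 0.5 with the true level differed between outer thirds at p<0.05 in about 5% of null trials at r = 0.5, 0.8 and 0.9, which is the nominal rate.

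**Whether baseline-adjusted regression cures it.** In the same model, regressing the 3-month value on the baseline value plus that trait flagged the trait in about a third of null trials at r = 0.5, 21% at 0.8 and 14% at 0.9. A noisy baseline leaves residual confounding by the true level. Such a regression shows prognosis, not drug benefit.

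**The case against.** The strongest reply is that the protocol does not write this analysis out. The sentence stands under expected results, is hedged with a probability word, and fixes no response variable, cut-off or test. Section 7 contains no responder comparison, and a SAP that is not shown may specify one. Anatomy, type of Fontan connection, age or sex would be natural readings of the characteristics meant. This stands as far as it goes: VO2peak change and thirds are assumptions made here, and the size of the artefact depends on them. But section 8 does state the conclusion to be drawn. With one value before, one after and no untreated Fontan group, no SAP can make that conclusion follow.

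The correlation of 0.5 is also a planning value, not a measured test-retest reliability. That stands too, which is why the range is shown.

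Three stronger readings are tempting and not supported:
- *Anything correlated with baseline will be falsely selected.* A stable trait tied only to the true level is not, as the working shows. An association between such a trait and change could still reflect natural course rather than the drug.
- *Patient selection is the stated purpose.* None of the five objectives in section 2, nor the main objective in the Summary, mentions it. It is an expected payoff in the Summary, section 1 and section 8.
- *The main before-after comparison is biased in the same way.* The eligibility criteria do not select on a low baseline value, so this mechanism leaves the mean change alone.

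**Conclusion.** The point holds in limited form. The claim that a best-versus-least comparison identifies who will profit from enalapril cannot be supported by this design, whatever the analysis. That part rests on the design alone.

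The size of the artefact rests on assumptions: response is VO2peak change, outer thirds are compared, and there is no drug effect. With the plan's SD of 6.8 and correlation of 0.5, the baseline gap is about 7.4 ml/kg/min and appears significant in about 92% of trials of 52. This falls to about 53% at a correlation of 0.8 and 29% at 0.9. The direction is the same for any correlation below 1.

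The damage is confined to the baseline of the response variable and measures sharing its visit-to-visit fluctuation. The sample size and the mean before-after test are untouched. This should be fixed, but it does not threaten the main comparison.

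**What to change.** 1. In section 8, label the responder comparison exploratory and descriptive, and delete the claim that it identifies the patients who will profit from enalapril.
2. State there that the baseline value of the response variable, and measures sharing its visit-to-visit fluctuation, will not be used as profiling characteristics.
3. In the Summary and at the end of the enalapril part of section 1, soften the patient-selection statements to hypothesis-generating.
4. If the 3-month value is regressed on baseline plus a characteristic, report the result as prognosis under treatment only. Do not present it as a cure, since it flags stable prognostic traits in about 14% to one third of null trials in the settings above.

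The cost is wording, plus giving up a claim the data could not carry. Keeping the claim would need a different design: an untreated or placebo Fontan comparison with a test of treatment-by-characteristic interaction.

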## **9. Administrative aspects of participants data**

All the data of all participants that will be collected during this study will be treated anonymously and confidentially.

### Confidentiality of participants data

Each study subject will receive a specified code that will be connected to the study data. This will be done to protect the privacy of each participant. This specific code will not consist of personal information that can lead to the study participant. Only the responsible- and principle investigators will have the key of the code to know which code stands for which participant. The key of this code is safely stored at the local institution where the research is carried out. Data of this study can be used in reports or scientific publications, but data will then still not be traceable to individual participants.

